This observational study seeks to address the unmet need for robust data linking perioperative platelet function test (PFT) results with clinical outcomes following CABG. The primary objective of this study is to determine the association between perioperative platelet function test results and clinical outcomes, including major adverse cardiovascular and cerebrovascular events (MACCE), postoperative bleeding, and the need for surgical re-exploration. In this study, MACCE is defined as a composite of myocardial infarction, non-fatal stroke, and cardiovascular death, assessed at 30 days and one year following CABG. The secondary objectives include assessing the prevalence of aspirin and clopidogrel resistance in CABG patients using platelet mapping, identifying demographic and clinical predictors of antiplatelet resistance—such as age, sex, diabetes, renal function, ethnicity, BMI, and surgical technique—and evaluating temporal trends in platelet responsiveness from the preoperative baseline through early and late postoperative periods. Additionally, the study will explore the relationship between high platelet reactivity and the need for postoperative escalation of care, including ICU readmission, inotropic support, and transfusions. Lastly, it will assess the feasibility of integrating PFT into the perioperative care pathway to support individualized antiplatelet management in future interventional studies.

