#### 2.1.1. Overall Design

The study will be conducted at a single tertiary NHS cardiac surgery centre, enrolling 100 patients who will receive standard perioperative and postoperative care according to institutional and national guidelines. No study drug or investigational device will be tested. The study aims to generate real-world data that may inform future interventional trials or guideline updates regarding the role of PFT in optimizing antiplatelet therapy for surgical patients.

A formal sample size calculation was performed to ensure sufficient statistical power to detect meaningful variability in platelet function and its association with clinical outcomes. Assuming a moderate effect size (Cohen’s d = 0.5), a two-sided alpha level of 0.05, and 80% statistical power, the minimum required sample size for comparison of platelet function measures was estimated at 63 patients.

To account for an anticipated attrition rate of approximately 20%, due to loss to follow-up or incomplete PFT across multiple perioperative timepoints, the adjusted minimum sample size was calculated to be approximately 80 patients. To further enhance robustness and allow for exploratory subgroup and longitudinal analyses, a final target sample size of 100 patients was selected.

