#### 2.7.4. Primary Endpoint Analysis

The primary objective of this study is to evaluate the association between platelet function test results and clinical outcomes in patients undergoing elective and urgent CABG.

Summary Measures

Platelet function results will be summarized as mean ± standard deviation or median with interquartile range (IQR), depending on data distribution, for:AA channel (aspirin response)ADP channel (clopidogrel response)

Clinical outcomes, including MACCE, bleeding, re-exploration, and transfusion, will be reported as frequencies and proportions.

Method of Analysis

Correlation analysis: Pearson’s correlation for normally distributed data, Spearman’s rank correlation for non-parametric dataLogistic regressionEstimates the odds of postoperative events based on platelet resistance status (resistant vs. non-resistant)Adjusts for potential confounders (age, diabetes, renal function, surgical factors)Hierarchical data structure: Generalized estimating equations (GEE) or mixed-effects models will be used to account for repeated measures of platelet function over time.

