#### 2.7.9. Handling of Multiplicity

No formal adjustments for multiple comparisons will be made, as these analyses are exploratory. All *p*-values will be interpreted cautiously, with emphasis placed on effect size and confidence intervals.

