### 3.2. Platelet Function and Clinical Outcomes

Platelet function test results will be analyzed at three timepoints: preoperative baseline, postoperative discharge, and six-week follow-up. The degree of platelet inhibition will be reported as percentage inhibition in response to arachidonic acid and adenosine diphosphate pathways, reflecting aspirin and clopidogrel effectiveness, respectively.

The prevalence of aspirin and clopidogrel resistance in the study population will be determined based on predefined cutoff values from the TEG6s Platelet Mapping system. Differences in platelet responsiveness between groups will be evaluated using repeated measures analysis of variance or non-parametric alternatives, depending on data distribution.

The primary analysis will assess correlations between platelet function test results and major adverse cardiovascular and cerebrovascular events, including myocardial infarction, stroke, cardiovascular death, postoperative bleeding complications, and the need for surgical re-exploration. Univariate correlations will be explored using Pearson or Spearman correlation coefficients, while logistic regression models will estimate the odds ratios for adverse outcomes associated with platelet resistance.

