## 7. Future Directions

Inter-individual variability in platelet responsiveness is influenced not only by clinical and perioperative factors but also by genetic determinants. Single nucleotide polymorphisms affecting platelet receptor pathways and antiplatelet drug metabolism—most notably variants in genes such as CYP2C19 involved in clopidogrel activation—have been shown to contribute to reduced antiplatelet efficacy and adverse cardiovascular outcomes. Integration of pharmacogenomic testing with platelet function assessment may therefore offer a more comprehensive approach to individualized antiplatelet therapy. Although genetic testing was beyond the scope of the present study due to its observational design and regulatory considerations, future studies incorporating combined platelet function and pharmacogenomic profiling may further refine risk stratification and therapeutic decision-making in CABG patients.

Should the study demonstrate a robust correlation between perioperative platelet function and postoperative outcomes, the findings may pave the way for future large-scale trials assessing the clinical utility of PFT-guided antiplatelet strategies. Specifically, randomized investigations evaluating tailored therapy based on individual platelet reactivity profiles could help bridge the existing gap between mechanistic understanding and therapeutic decision-making. Additionally, long-term follow-up studies examining the durability of platelet function trends beyond the immediate postoperative phase may further elucidate the trajectory of antiplatelet resistance and refine patient management strategies.

Taken together, this study is expected to contribute meaningful insights into the evolving field of CABG pharmacotherapy. By systematically analyzing platelet function patterns and correlating them with postoperative outcomes, this investigation holds the potential to advance precision medicine in surgical myocardial revascularisation, ultimately improving patient safety and optimizing antiplatelet management in CABG populations.

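### For continuous % inhibition, the only named measure of association with yes/no events is a correlation coefficient whose size depends on how frequent the event is

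*Protocol article*

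**What the plan says.** Section 3.2 of the protocol article sets out the primary analysis: "The primary analysis will assess correlations between platelet function test results and major adverse cardiovascular and cerebrovascular events", with bleeding and re-exploration in the same list. The method follows: "Univariate correlations will be explored using Pearson or Spearman correlation coefficients". The same sentence then adds logistic regression, giving odds ratios for adverse outcomes by platelet resistance.

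Section 2.7.4 names the same two methods. It chooses Pearson or Spearman according to whether the data are normally distributed. Its logistic model takes resistance status, in two categories, as the exposure and adjusts for age, diabetes, renal function and surgical factors. GEE or mixed models are named only to handle repeated platelet measurements.

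The scales of the two sides are also stated. For the marker, section 3.2 says "The degree of platelet inhibition will be reported as percentage inhibition in response to arachidonic acid and adenosine diphosphate pathways", which is continuous. For the outcomes, section 2.7.4 says "Clinical outcomes, including MACCE, bleeding, re-exploration, and transfusion, will be reported as frequencies and proportions", so each is a yes/no variable per patient. The Introduction confirms this for the main one: "MACCE is defined as a composite of myocardial infarction, non-fatal stroke, and cardiovascular death, assessed at 30 days and one year following CABG".

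On interpretation, section 2.7.9 makes no multiplicity adjustment and says p-values will be read cautiously, "with emphasis placed on effect size and confidence intervals".

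**The concern.** A correlation coefficient between a continuous marker and a yes/no event does not run up to 1. Its ceiling falls as the event becomes less frequent, so one coefficient mixes two things: how well the marker separates patients with and without the event, and how many patients had it. The rule for choosing between Pearson and Spearman does not help, because it turns on normality and a yes/no outcome is never normal.

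This matters because section 2.7.9 directs the reader to the size of the effect, and the Discussion asks whether platelet function testing can stratify risk reliably. If MACCE is infrequent, a useful marker would show a coefficient that looks negligible. If bleeding is more or less frequent than MACCE, the two coefficients would differ even where the test predicts both equally well.

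**Working it through.** **Inputs.** The article states no correlation, AUC or event rate, so it has no figure of its own to reproduce on this point. Its only effect size is in the sample size paragraph of section 2.1.1: "Assuming a moderate effect size (Cohen’s d = 0.5), a two-sided alpha level of 0.05, and 80% statistical power". The event rates p below are assumptions, shown as a range. The sign of the association is ignored.

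**Step 1. Spearman against a yes/no event.** With N patients and no ties in the marker:
- mean rank in event patients minus mean rank in the others = N·(AUC − ½);
- SD of the ranks ≈ N/√12;
- SD of the yes/no variable = √(p(1 − p)).

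Hence Spearman = (AUC − ½)·√12·√(p(1 − p)) = (2·AUC − 1)·√(3p(1 − p)).

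The ceiling, at AUC = 1, is √(3p(1 − p)). At p = 5% this is √(3 × 0.05 × 0.95) = √0.1425 = 0.38. For AUC 0.75 the multiplier is 2 × 0.75 − 1 = 0.5.

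| Assumed event rate | Spearman, perfect separation | Spearman, AUC 0.75 |
|---|---|---|
| 5% | 0.38 | 0.19 |
| 10% | 0.52 | 0.26 |
| 20% | 0.69 | 0.35 |
| 30% | 0.79 | 0.40 |

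**Step 2. Pearson against a yes/no event.** For a marker that is normal overall, the ceiling is φ(z_p)/√(p(1 − p)): 0.47 at 5%, 0.59 at 10%, 0.70 at 20%. For two normal groups with equal SD and standardised difference d, r = d/√(d² + 1/(p(1 − p))), AUC = Φ(d/√2), and the odds ratio per within-group SD is exp(d).

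| Marker | AUC | OR per SD | r at 5% | r at 10% | r at 20% | r at 50% |
|---|---|---|---|---|---|---|
| d = 0.5 (the size assumed in 2.1.1) | 0.64 | 1.65 | 0.11 | 0.15 | 0.20 | 0.24 |
| d = 1 | 0.76 | 2.72 | 0.21 | 0.29 | 0.37 | 0.45 |

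Along each row the AUC and odds ratio are fixed. Only the correlation moves.

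**Step 3. Check at the planned sample size.** Take 100 patients ordered on a normal marker and give the event to the highest-ranked. With 5 events, Pearson is 0.47 and Spearman 0.38; with 10 events, 0.59 and 0.52; with 20 events, 0.70 and 0.69. These agree with the formulas.

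**Step 4. Is the test affected?** In one simulated set of 100 patients with 10 events, the Pearson p-value and the pooled t-test p-value were identical (0.00217). Testing is sound; the scale of the estimate is the problem.

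**The case against.** The strongest reply is that logistic regression is also part of the primary analysis, in the same sentence of section 3.2 and with adjustment in section 2.7.4. An odds ratio has no such ceiling, and the correlations are described as univariate and exploratory. This stands in part: a reader might infer that the primary analysis rests on correlation alone, and it does not. But the logistic model uses only resistant versus non-resistant status, so it says nothing about continuous % inhibition.

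Three other strong readings are tempting and fail.
- Section 7 says "Should the study demonstrate a robust correlation between perioperative platelet function and postoperative outcomes", which might be read as a trigger for further trials. It is discussion prose with no threshold and no named coefficient, and the article uses correlation and association interchangeably.
- A reader might infer that outcomes will be ranked by coefficient, or that section 2.7.9 singles the coefficient out. Neither is stated; that section speaks of effect sizes in general, and the odds ratio is one too.
- A reader might infer that MACCE is known to be rare here. The article gives no rate, and at 20% the loss is milder (r = 0.37 for AUC 0.76).

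It is also fair that the number of events limits precision under any metric. At an assumed 5 events in 100, an AUC of 0.75 has a Hanley–McNeil standard error of about 0.13, so a 95% interval of 0.75 ± 1.96 × 0.13, roughly 0.50 to 1.00.

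Finally, one could leave discrimination measures to an unseen analysis plan. But the point is not an omission: the article positively names a coefficient for these outcomes, and that choice fits them poorly.

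**Conclusion.** The point holds, limited to the size and comparability of the reported effect for continuous % inhibition. At an assumed 5% event rate, even a perfect marker reaches only 0.38 on Spearman or 0.47 on Pearson. The same AUC of 0.75 is reported as a Spearman of 0.19 at 5% and 0.40 at 30%. How far MACCE is understated depends on its rate, which the article does not give. The lack of comparability arises whenever outcomes differ in frequency, unless their rates are symmetric about 50%. The Pearson figures also assume a normal marker (for the ceilings) or normal groups with equal SD (for the d values); the Spearman formula needs only an untied marker. There is no invalid test, no error-rate problem and no faulty decision rule.

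**What to change.** In sections 2.7.4 and 3.2, for every binary outcome, replace the correlation coefficient with two measures for continuous AA or ADP % inhibition, each with a 95% CI:
- the odds ratio per SD (or per 10 points) from logistic regression, penalised if events are few;
- the AUC.

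Keep Pearson or Spearman for pairs of continuous variables, such as % inhibition and length of stay, where the normality rule makes sense. Keep the planned odds ratio for resistance status. Section 7 needs no change beyond wording consistent with the new measures, since it sets no criterion.

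The cost is wording only; the data collected are the same. The small downside is that with few events the intervals will be wide, which is an honest picture of what 100 patients can show.

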### 3.3. Secondary Analyses

Secondary analyses will investigate potential predictors of platelet function variability, including demographic and clinical factors such as diabetes status, renal function, smoking history, and surgical approach. Multivariable regression models will be employed to adjust for key covariates and assess independent associations with platelet responsiveness.

Additionally, the feasibility of integrating PFT into routine perioperative workflows will be examined. The study will evaluate whether PFT results influence clinical decision-making, including modifications in antiplatelet therapy or postoperative management.

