## Abstract

Background: Coronary artery bypass grafting (CABG) is a well-established revascularization strategy for patients with multivessel coronary artery disease. The effectiveness of CABG is significantly influenced by antiplatelet therapy aimed at maintaining graft patency and reducing thrombotic complications. However, substantial inter-individual variability exists in platelet function responses to standard therapies such as aspirin and clopidogrel, leading to antiplatelet resistance. This variability has been linked to increased risks of myocardial infarction, stroke, and early graft failure. Platelet function testing (PFT) offers a potential strategy to identify resistance and guide more personalized antiplatelet therapy. This study aims to evaluate the association between perioperative platelet function test results and clinical outcomes following CABG. By assessing platelet responsiveness at multiple timepoints and correlating findings with postoperative events, the study seeks to determine whether PFT can stratify risk and improve patient management. Methods: This is a prospective, single-centre, observational cohort study conducted at a tertiary NHS cardiac surgery centre. Patients having elective or urgent isolated CABG will be enrolled and undergo perioperative PFT using the TEG6s system. Clinical outcomes will be monitored for 12 months postoperatively, with primary endpoints assessing the correlation between platelet function results and major adverse cardiovascular and cerebrovascular events (MACCE). Secondary endpoints will include the prevalence of antiplatelet resistance, demographic predictors, and the feasibility of integrating PFT into clinical workflows. Results: This study will report the prevalence of aspirin and clopidogrel resistance in CABG patients based on TEG6s PFT, as well as the correlation between platelet function results and MACCE, postoperative bleeding, and the need for surgical re-exploration. Additionally, it will examine the associations between demographic and clinical factors—such as diabetes status, renal function, BMI, and surgical technique—and variability in platelet responsiveness. The feasibility of incorporating PFT into perioperative workflows will also be evaluated, assessing whether results could support personalized antiplatelet management in future clinical trials. Conclusions: Findings from this study will provide real-world evidence regarding platelet function variability in CABG patients and suggest that PFT may identify those at increased risk of thrombotic complications. This exploratory analysis supports the need for larger interventional trials aimed at optimizing individualized postoperative antiplatelet therapy to improve surgical outcomes.

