#### 2.1.2. Study Design Summary

Design type: Prospective, observational, non-randomised, non-blindedBlinding: PFT results will be blinded from the treating surgical team to avoid influencing management decisions. Investigators and participants will have access to clinical data.Control arm: Not applicableRandomisation: Not applicableSetting: Single tertiary NHS cardiac surgery centreRecruitment target: 100 patientsFollow-up: From preoperative baseline until 30 days post-CABG, with planned 1-year MACCE follow-up via digital health records

This design was chosen to capture the natural variability in platelet responsiveness and correlate these patterns with real-world surgical outcomes. Importantly, the study does not introduce any confounding influence of investigational treatments or unblinded interventions, ensuring validity in evaluating platelet function and postoperative risk stratification. Figure 1 summarizes the study design.

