#### 2.1.3. Treatment and Rationale

As a non-interventional observational study, no study-specific treatment will be administered, and participants’ standard perioperative and postoperative care will remain unaltered.

All antiplatelet therapy will be prescribed at the discretion of the treating surgical teams, following institutional protocols and national guidelines. The study does not involve randomisation, dose escalation, or therapeutic modifications based on PFT results. Instead, it aims to evaluate the association between naturally occurring variability in platelet reactivity and clinical outcomes under standard care conditions.

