#### 2.7.7. Intention-to-Treat Statement

Since this is a non-randomized observational study, an intention-to-treat analysis is not applicable. Analyses will be conducted on participants with complete platelet function and outcome data.

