#### 2.7.8. Secondary Endpoint Analysis

Analyses of secondary endpoints are exploratory and hypothesis-generating, as the study is not powered for statistical significance in these measures. Findings will guide future studies.

Variability in Platelet Function

Objective: Assess inter-individual variability in platelet inhibition across timepoints.Analysis:
Continuous values (% inhibition) summarized at baseline, discharge, and 6 weeksRepeated measures ANOVA or Friedman test for within-patient changesBoxplots and line graphs used for visualization

Prevalence of Platelet Resistance

Objective: Determine the proportion of patients with inadequate platelet inhibition.Analysis:
Categorical resistance status reported for each timepoint with 95% confidence intervalsChanges in resistance status analyzed using McNemar’s test for paired categorical data

Demographic and Clinical Predictors of Platelet Function

Objective: Explore associations between patient characteristics and platelet responsiveness.Analysis:
Univariable and multivariable linear regression for continuous % inhibition outcomesConsidered variables: age, sex, BMI, renal function, diabetes, and number of graftsSelection guided by clinical relevance and statistical significance (*p* < 0.1)

Impact of Platelet Resistance on Clinical Decision-Making

Objective: Evaluate whether platelet resistance influences treatment decisions, including DAPT use and discharge timing.Analysis:
Comparisons of DAPT prescription rates between resistant and non-resistant patients using chi-square or Fisher’s exact testLogistic regression to explore predictors of treatment decisions if data allows

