## 6. Study Limitations

As an observational study, this research does not involve direct therapeutic interventions by the study team. However, PFT results will be conveyed to the clinical team caring for the patient, who may modify treatment based on their clinical judgment. The study itself will generate valuable data regarding platelet function trends and potential predictors of poor outcomes, contributing to a better understanding of antiplatelet resistance without directly altering patient management within the study framework.

This study does not include immediate postoperative PFT upon arrival to the intensive care unit. While such measurements may offer mechanistic insights, discharge sampling was selected to balance clinical feasibility, patient safety, and assessment of stabilized platelet function following early recovery and antiplatelet therapy initiation.

Additionally, as with all studies incorporating PFT, variability in assay methodology and interpretation remains a challenge, given the lack of universal standardization across testing platforms [6]. Furthermore, the study is designed to evaluate platelet function within a defined perioperative timeframe, yet long-term outcomes beyond the study period may also be influenced by additional variables such as medication adherence, comorbid conditions, and secondary prevention strategies.

While venesection poses minimal risk, the additional blood sampling may introduce slight inconvenience for participants, although efforts have been made to integrate sample collection within routine clinical care.

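### The analysis of whether PFT results influence treatment decisions is not supported by the stated design and should not stand in for the feasibility endpoint

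*Protocol article*

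**What the plan says.** Feasibility of building PFT into the care pathway is a listed secondary endpoint (section 2.6.2). The Abstract describes it this way: "The feasibility of incorporating PFT into perioperative workflows will also be evaluated, assessing whether results could support personalized antiplatelet management in future clinical trials". Section 3.3 says that "the feasibility of integrating PFT into routine perioperative workflows will be examined. The study will evaluate whether PFT results influence clinical decision-making". No other evaluation is named beside feasibility there.

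Section 2.7.8 has four headed analyses: variability, prevalence, predictors, and the effect of resistance on clinical decisions. The objective of the fourth is "Evaluate whether platelet resistance influences treatment decisions, including DAPT use and discharge timing". Its method is a chi-square or Fisher's exact comparison of DAPT rates by resistance status, with logistic regression if the data allow.

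Three passages govern whether prescribers can see or act on a result:
- Section 2.1.2: "PFT results will be blinded from the treating surgical team to avoid influencing management decisions".
- Section 2.1.3: "The study does not involve randomisation, dose escalation, or therapeutic modifications based on PFT results".
- Section 6: "PFT results will be conveyed to the clinical team caring for the patient, who may modify treatment based on their clinical judgment".

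On the analysis set, section 2.7.7 says "Analyses will be conducted on participants with complete platelet function and outcome data". Section 2.7.2 separately commits to reporting the numbers approached, consented, excluded with reasons, tested at each timepoint, included in endpoint analyses, and lost to follow-up.

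**The concern.** A result can influence a decision only if the person deciding knows it. The plan sets out to measure that influence, while its design summary withholds results precisely so that there is none, and its limitations section then says that results are passed on. As written, a reader of the final report could not tell what a difference in DAPT rates means.

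The same analysis is the only one named next to feasibility. Feasibility is meant to support future PFT-guided studies, so a planner would want to know whether samples were obtained on schedule, run within the four-hour limit of section 2.5.2, and gave usable results. A prescribing comparison answers none of these. The complete-data rule, read literally, would also apply to any feasibility rate, and there it cannot work.

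**Working it through.** **Step 1. Can the comparison show influence? Take each disclosure reading in turn.**

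*Results hidden (sections 2.1.2 and 2.1.3).* Section 2.1.3 leaves antiplatelet prescribing to the treating surgical teams, and section 2.1.2 keeps the results from them. A path from PFT result to prescription is then closed by design. A difference in DAPT rates by resistance status can still appear, for other reasons:
- Treatment affects the test. The Introduction says that clopidogrel blocks P2Y12, and section 2.7.4 uses the ADP channel as the measure of clopidogrel response. If DAPT means aspirin plus clopidogrel, the two agents listed in section 2.1.4, patients on DAPT should show more ADP inhibition and be classed as resistant less often. For the discharge and six-week tests, the arrow can run from prescription to resistance status.
- Shared causes. For the baseline test, postoperative DAPT cannot act backwards, but preoperative treatment and patient characteristics such as diabetes or renal function may relate to both variables.
- Discharge timing has a similar problem. Under section 2.5.1 the second test is taken at day five to seven, or earlier if the patient leaves earlier, so the discharge date helps set the test date.

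*Results released (section 6).* Influence is now possible. Even so, a comparison by resistance status mixes decisions made before and after a result was known, and the treatment-to-test path remains. If it were clean, it would measure whether clinicians act on results. That is uptake, not deliverability.

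On neither reading does the planned comparison serve as an evaluation of feasibility.

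**Step 2. What does the complete-data rule do to a completion rate?**

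Inputs from section 2.1.1: target 100 patients; attrition of about 20%, which combines loss to follow-up and incomplete PFT. The split is not given. The plan states no feasibility figure, so there is none to reproduce.

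Assumption for illustration: all of the 20% is incomplete PFT.
- Over all enrolled: 100 × (1 − 0.20) = 80, so 80/100 = 80%.
- Within the complete-data set: 80/80 = 100%, because completeness is the entry condition.

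The Wilson 95% interval is [p + z²/2n ± z√(p(1−p)/n + z²/4n²)] / (1 + z²/n). With p = 0.80, n = 100 and z = 1.96:
- z²/n = 0.0384, and z²/2n = 0.0192
- centre = 0.8192 / 1.0384 = 0.789
- half-width = 1.96 × √(0.0016 + 0.000096) / 1.0384 = 0.078
- interval = 71% to 87%

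Range over other completion rates, because the split is unknown:

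| Completed of 100 | Rate | Wilson 95% CI | Rate in complete-data set |
|---|---|---|---|
| 70 | 70% | 60% to 78% | 100% |
| 80 | 80% | 71% to 87% | 100% |
| 90 | 90% | 83% to 94% | 100% |

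Whatever the true rate, the complete-data set returns 100%.

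**The case against.** Four objections have weight.

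*Influence may be possible.* A reader might infer from section 2.1.2 that PFT results can never affect decisions in this study. The documents do not support that, because section 6 says results are conveyed. Section 2.1.3 can also be read as saying only that the study mandates no treatment change, which would be compatible with section 6. The sharper clash is between sections 2.1.2 and 6. One could try to separate the surgical team from the clinical team, but the article draws no such line and gives prescribing to the surgical teams. The conflict therefore stands, and which passage governs is open.

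*Decision influence is not declared to be the feasibility measure.* Section 3.3 places two sentences side by side, and section 2.7.8 gives decision impact its own heading. The endpoint is also framed around supporting individualised management, so uptake may be a legitimate part of it. This is right as far as it goes. The link is an inference. What can be said is that no other evaluation is named beside feasibility and that feasibility has no item of its own in section 2.7.8.

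*Failed tests are not lost.* A reader might infer that section 2.7.7 removes them from the report. It does not. Section 2.7.2 reports completion at each timepoint and lists the analysed number separately, and no section proposes a completion rate inside the complete-data set. What remains is that nothing ties those counts to the endpoint or exempts it from section 2.7.7.

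*Detail may sit elsewhere.* This is a condensed article. The absence of a feasibility metric or a progression threshold is not a fault, and none is claimed.

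**Conclusion.** The point holds in this limited form. The decision-influence analysis in sections 2.7.8 and 3.3 rests on a disclosure rule that the article states in two incompatible ways. If results are hidden, the DAPT comparison cannot show influence. If they are released, it shows uptake at best. It should not be read as the feasibility result under either rule. Separately, section 2.7.7 has no exception for feasibility, and a completion rate in that set is 100% by construction.

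The size is illustrative: 80% (71% to 87%) against 100%, if the whole of the anticipated attrition is incomplete PFT, with intervals running from 60% to 78% at 70% completion up to 83% to 94% at 90%. The argument about ADP inhibition assumes that DAPT includes clopidogrel. These are exploratory secondary analyses, so the primary result is not affected. The issue still merits correction, because feasibility is what the study offers to planners of later trials.

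**What to change.** 1. Reconcile sections 2.1.2 and 2.1.3 with section 6 on who sees PFT results and when. Which rule applies is for the sponsor and investigators to settle.
2. Drop the objective on influence over treatment decisions, or restrict it to decisions made after a documented release of a result. Otherwise keep the DAPT comparison as a descriptive association, with no claim about direction.
3. Separate the two sentences in section 3.3, so that the DAPT comparison is not taken as the feasibility evaluation.
4. Report feasibility from the counts already promised in section 2.7.2, with all consented patients as the denominator, and state that the complete-data restriction of section 2.7.7 does not apply to that endpoint.

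The cost is small. Sample size and testing schedule are unchanged, and most of the work is wording. Keeping the decision objective would need a record of when each result was released. The reported completion figure will be less favourable than one taken from the complete-data set.
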